### **3. Statistical Methods**

### 3.1. Interim Analyses

The protocol stated that a treatment-blind statistician may carry out interim quality checks and efficacy analysis. No interim analyses were needed, and none were done.

### 3.2. Statistical Analyses

A treatment-blind statistician will analyze the data after completion of follow-ups for all recruited participants using SPSS for Windows, version 20.0 (IBMCorp., Armonk, N.Y.).

Like the Guo et al. (2015) trial, we will use independent-sample t-tests, Mann-Whitney U tests, and chi-square tests, to compare sociodemographic and clinical characteristics, discontinuation, response and remission rates, and side effects as appropriate. Full intent-to-treat analyses will be carried out to determine all-cause discontinuation. Estimated time from randomization to response and remission will be calculated using Kaplan-Meier survival analyses, and a comparative analysis will be facilitated using the Cox proportional hazards regression model. Analysis of covariance will be used to compare the changes in HDRS scores between the two groups. Additional subgroup analysis might be carried out to understand group-differences due to age, gender, duration of illness, and number of previous episodes. The significance threshold will be  $p < 0.05$  (two-tailed) for all analyses.

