Major treatment guidelines from high-income countries emphasize the importance of 'Measurement-Based Care' (MBC), which utilizes outcomes based on validated clinical instruments to

guide treatment decisions (Aboraya et al., 2018; Gelenberg, 2010; Kennedy et al., 2016). This concept was derived from the stepwise treatment algorithm developed through the Sequenced Treatment Alternatives to Relieve Depression (STAR\*D) trial (Trivedi, 2009; Trivedi, Rush, et al., 2006; Trivedi & Daly, 2007). The large-scale trial funded by the US National Institute of Mental Health examined treatment options in an algorithmic manner with the aim to guide the next steps for treatment of patients with MDD who have an inadequate response to an antidepressant. The trial reported significantly improved outcomes, better-informed treatment decisions and greater remission rates in patients with chronic depression. Similarly, in a study of 120 patients with moderate to severe MDD in China, significantly more patients receiving MBC achieved response (86.9% compared with 62.7%) and remission (73.8% compared with 28.8%) compared to those receiving standard care (Guo et al., 2015). Time to response and remission were significantly shorter with MBC (for response, 5.6 weeks compared with 11.6 weeks, and for remission, 10.2 weeks compared with 19.2 weeks). There was also a significantly larger decrease in Hamilton Depression Rating Scale (HDRS) scores (-17.8 compared to -13.6) in the MBC group. The MBC group had significantly more treatment adjustments (44 compared with 23) and higher antidepressant dosages from week 2 to week 24 (Guo et al., 2015). MBC has also been found to help patients gain insight into their illness course; those who completed self-reports of depressive symptoms expressed that the measures allowed them to quantify their symptoms and gain a better understanding of their experience with depression (Dowrick et al., 2009). The better educated patients are about these measurements, the more they adhere to a treatment plan (Trivedi et al., 2020). MBC may also be a valuable tool for facilitating collaborative care among providers within and across organizations (Katon et al., 2010). Given MBC's potential to improve outcomes, it may be one of the minimal interventions necessary for maximal improvement in clinical outcomes in patients with MDD (R. Kessler & Glasgow, 2011).

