## Methods

The aim of this trial is to determine the efficacy and safety of MBC in patients with MDD in comparison with standard care in Pakistan. In order to reduce the variance found in treatment-as-usual and isolate the impact of MBC, standard care for this trial will limit medication choices to either paroxetine or mirtazapine (as per previously published trials). We hypothesize that, compared to standard care group, the MBC group will have significantly higher rates and shorter times to response and remission, along with lower rates of dropout and side effect burden.

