## **Assessment Procedure**

This trial will include two experienced treatment-blind assessors at each site, who will independently administer the mentioned outcome measures at baseline and at 2, 4, 8, 12, and 24 weeks. The research coordinator at each site will advise and remind patients at each visit about non-disclosure of their treatment groups to the assessor.

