We do not anticipate any major risks related to the intervention. However, we acknowledge that potentially vulnerable people with mental illness will be participating in the trial. Some topics discussed or questions asked in the sessions/assessments may cause distress, and in such instances, appropriate support will be provided. We will map available mental health resources ensuring pathways to care. The research team has considerable clinical and research experience, including the management of difficult situations arising in research interventions and interviews. In case participant recruited to this study experience active suicidal ideation or subsequently identified as needing more intensive treatment will be appropriately referred for psychiatric evaluation and treatment. Patients will be removed from the study if they report suicidal attempt, became pregnant, developed a severe medical condition, or suffered from newly emerging side effects that they find intolerable and that could not be managed. Patients who will be removed from the study will receive antidepressant treatment as appropriate as part of clinical care. Research staff will be provided with regular supervision throughout the duration of the project. We already have study protocols in place that include details about how to manage difficult situations arising in research, safety and lone working arrangements. In the event of any study-related injury or adverse event, intervention and treatment will be available from medical staff. Any adverse events will be reported to the REB within the required timeframe.

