### **2. Outcomes**

A form will be designed to collect sociodemographic and clinical characteristics from the medical records, and this information will be confirmed in a clinical interview. HDRS scores will be used to inform two primary outcomes measures: estimated time from randomization to response (defining response as  $\geq 50\%$  reduction in HDRS from baseline) and remission (defined as HDRS score  $\leq 7$ ) (Hamilton, 1960).

Secondary outcome measures will include changes in severity of depressive symptoms (HDRS score). An additional checklist with six common side effects (dry mouth, diarrhea or constipation, dizziness or drowsiness, loss of appetite or nausea, headache, and excessive sweating); and the FISBER, will be used to measure side effects at each treatment visit. The pill count method will be used to measure treatment adherence.

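### The ANCOVA of HDRS change has no time point, analysis population or missing-data rule, though dropout is expected to differ by arm; a mixed model on all scheduled visits is the better planned analysis

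*Combined protocol and SAP*

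**What the plan says.** - **Analysis.** SAP section 3.2: "Analysis of covariance will be used to compare the changes in HDRS scores between the two groups". The Statistical analysis section of the protocol plans the same method for HDRS and YMRS. Neither names the visit, the covariates, the patients included or the handling of missing scores.
- **Role.** HDRS change is a secondary outcome (SAP section 2). The two primary outcomes are times to response and remission, analysed by Kaplan-Meier and Cox methods.
- **Intent-to-treat.** The SAP's only such statement is "Full intent-to-treat analyses will be carried out to determine all-cause discontinuation". The protocol's version also covers discontinuation only, adding specific causes.
- **Expected dropout.** The hypothesis in the protocol Methods, repeated in SAP section 1, is higher and faster response and remission with MBC, "along with lower rates of dropout and side effect burden". No rates are given.
- **Removals.** Ethical and safety considerations: "Patients will be removed from the study if they report suicidal attempt, became pregnant, developed a severe medical condition", or had new side effects that were intolerable and unmanageable. HDRS assessment after removal is not described.
- **Visits.** Assessors "will independently administer the mentioned outcome measures at baseline and at 2, 4, 8, 12, and 24 weeks", so five post-baseline HDRS scores are scheduled per patient.

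**The concern.** A single-visit ANCOVA with nothing imputed can use only patients who have that visit's score. A patient who leaves after week 12 contributes nothing to a week-24 comparison, although four post-baseline scores are on file. If those who leave differ in outcome from those who stay, and more leave one arm, the remaining patients no longer represent the randomised groups. The trial predicts unequal dropout, and some of its removal reasons reflect clinical state, so both conditions are plausible here.

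The silence also leaves the choice of method open. Completer analysis, last observation carried forward (LOCF) and a likelihood model can give materially different estimates from the same data. At stake is the estimate for HDRS change, the trial's continuous measure of depressive severity.

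**Working it through.** **No figure to reproduce.** The plan states no number for this analysis and no expected dropout.

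**Input from the documents.** The Introduction reports, for the replicated trial, HDRS "scores (-17.8 compared to -13.6) in the MBC group". The difference is -17.8 - (-13.6) = -4.2, used below as the true value.

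**How the bias arises.** For each arm, let s be the mean change among patients with a week-24 score minus the mean change among all randomised patients. The completer comparison then estimates, apart from baseline adjustment,

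true difference + (s in MBC - s in standard care).

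- Dropout unrelated to outcome: both s are 0, so there is no bias, however unequal the dropout.
- Worse patients leave: both s are negative, and more so where more leave. With more dropout in standard care the bracket is positive and -4.2 shrinks towards 0.
- Improved patients leave: the signs reverse and the difference is exaggerated.

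**Assumptions not in the documents.** Baseline mean 24 and SD 4; post-baseline SD 6, 7 or 8; correlation 0.75 between adjacent visits, decaying with distance; permanent dropout; log-odds of leaving raised by 1.0 per SD of worse HDRS. Dropout depends either on the last observed score (missing at random, MAR; loss before week 2 was random in these runs) or on the current, unseen score (missing not at random, MNAR). There were 200,000 simulated patients per arm. The likelihood estimate was obtained by sequential regression within arm, which is maximum likelihood for permanent dropout. Differences of about 0.05 are simulation noise.

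Estimates at SD 7 (truth -4.2):

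| Dropout, standard care v MBC | Mechanism | Completer ANCOVA | Likelihood model | LOCF ANCOVA |
|---|---|---|---|---|
| 15% v 15% | MAR | -4.22 | -4.22 | -3.91 |
| 20% v 10% | MAR | -3.95 | -4.18 | -4.92 |
| 30% v 15% | MAR | -3.81 | -4.17 | -5.28 |
| 40% v 20% | MAR | -3.69 | -4.21 | -5.70 |
| 20% v 10% | MNAR | -3.85 | -4.01 | -4.76 |
| 30% v 15% | MNAR | -3.66 | -3.89 | -5.06 |
| 40% v 20% | MNAR | -3.48 | -3.76 | -5.40 |

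Over SD 6 to 8 with unequal dropout:

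- MAR: completers -4.01 to -3.65; likelihood -4.25 to -4.12.
- MNAR: completers -3.89 to -3.31; likelihood -4.02 to -3.63.
- LOCF, both mechanisms: -4.74 to -5.76, an overstatement of 0.54 to 1.56 points.

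**What the likelihood model leaves behind under MNAR.** At 30% v 15% and SD 7, the completer bias is 4.20 - 3.66 = 0.54 and the likelihood bias is 4.20 - 3.89 = 0.31. So 0.31/0.54 = 57% remains.

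**Strength of the link between severity and leaving.** Dropout 33% v 11%, SD 7, correlation 0.8, MAR:

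| Log-odds of leaving per SD of worse HDRS | Completer ANCOVA | Bias |
|---|---|---|
| 0 | -4.17 | 0.03 (noise) |
| 0.5 | -3.82 | 0.38 |
| 1.0 | -3.66 | 0.54 |
| 2.0 | -3.46 | 0.74 |

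In a run where improved patients left instead, the completer estimate was -4.93, beyond -4.2. The largest MAR bias found was 4.2 - 3.3 = 0.9 points, and it needs a strong link. At 11% v 8% dropout the bias was about 0.1.

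**The case against.** - **The text does not restrict the analysis to completers.** A reader might infer that it does, but the documents are silent. Completer analysis is what an ANCOVA does by default, and LOCF is not excluded. This stands, and it is why the defect is an unspecified rule rather than a stated wrong one.
- **The direction is not established.** A reader might conclude that the bias works against MBC. That holds only for completer analysis when worse patients leave standard care. With improved patients leaving, or LOCF under unequal dropout, the simulated bias favours MBC. This stands.
- **Patients may still be assessed.** The protocol intends 24 weeks of follow-up for everyone, so stopping medication need not mean a missing HDRS score. This stands in part: the removal rules concern leaving the study, and no assessment after removal is described.
- **Importance is limited.** HDRS change is secondary, the SAP does not rank its secondary outcomes, and the protocol calls the trial exploratory. This stands and limits the weight of the point.
- **The trial is a direct replication.** Replacing ANCOVA would cost comparability with the earlier trial. Keeping the ANCOVA as a supportive analysis meets this.

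**Conclusion.** The point holds as a gap in SAP section 3.2 for which a better method is available on data already scheduled. The analysis should change, but this is not a fatal defect.

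The size is uncertain. With a true difference of -4.2, SD 6 to 8, correlation about 0.8 and dropout from 11% v 8% to 33% v 11% (standard care v MBC), completer bias runs from about 0.1 to about 0.9 points under MAR. Under MNAR, over a comparable range of assumptions with worse patients more likely to leave, completer estimates ran from -4.2 to -2.8 and likelihood estimates from -4.25 to -3.3. Only the -4.2 comes from the documents, so the pattern deserves more trust than any single figure.

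Two stronger readings are not supported. A reader might infer that a repeated-measures model removes the bias. It does so under MAR; otherwise it only reduces it, and the removal reasons make MNAR plausible. A reader might also take the upper end, 0.9/4.2 = 21%, as the expected loss. It depends on a strong assumed link between severity and leaving, for which the documents give no evidence.

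**What to change.** In SAP section 3.2, while the statistician is still blind to which arm is which:

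1. **Main analysis of HDRS change.** Use a likelihood-based mixed model for repeated measures on all scores at weeks 2, 4, 8, 12 and 24, in all randomised patients with at least one post-baseline score. Include arm, visit, arm-by-visit, baseline HDRS, and the stratification factors site and sex. Use an unstructured covariance, with a named simpler structure if it does not converge. The week-24 contrast is the estimate. Do not use repeated-measures ANOVA, which drops incomplete cases.
2. **Supportive analysis.** Keep the week-24 ANCOVA for comparability with the replicated trial and state which patients it includes. It cannot serve as a check for MNAR: it needs a stronger missingness assumption than the mixed model, and in the MNAR simulations both were biased in the same direction.
3. **Sensitivity analysis.** Add a delta adjustment: shift the scores assumed for patients who leave by a stated range of amounts, separately by arm, and report where the conclusion changes.

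The cost is SAP wording and a little more analysis; the MIXED procedure in SPSS fits the model, and no new data are needed. The downside is that the main estimate is unbiased only under MAR, which is why the third step is needed.
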